## *6.4. Sample size calculation*

Given current usual care with pre-operative staging with CT of the thorax and abdomen and neo-adjuvant therapies, the expected occurrence of metachronous metastases is approximately 25%. Of these, the expected percentage of resected metastases in patients is 10% in the control group and 25% in the intervention group. Given a significance level of 5% and a power of 80%, 115 patients with metastases in both groups are needed. Given an expected recurrence rate of 25%, 460 patients per group are needed.

Because in this study the moment to start the intervention instead of patients will be randomized, we calculated a correction factor C. Assuming a standard deviation in the effect of hospitals on the outcome of 0.1, C has a value of 1.71. (van Houwelingen) Therefore about 800 patients per group are needed.

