*7.2.1.Procedure when CEA crosses the threshold value (see flowchart, addendum 2)*

Increase > 20% in 8 weeks > repetition of CEA measurement in 4 weeks, also measuring CRP level.

Increase in second measurement after 4 weeks > 10%, with a lower static threshold value of 2.5 ng/ml > outpatient clinic visit; if explanation of rise is clear from clinical reasons (ie., active infection): treat infection and re-assess CEA value after 4 weeks. If increase:

-> Evaluation by helical CT Thorax/abdomen within two weeks:

-> Outpatient clinic within 7 days after CT scan

At this visit an assessment is made evaluating

- The presence of resectable metastasis in liver or lung

- Physical signs suggesting other localizations of recurrent disease

- Fitness of the patient to undergo treatment of metastasis

When curable metastases are found and the patient can undergo metastasectomy

-> Treatment at own or referral centre according to the current standard

When irresectable metastases are found or the patient is unfit to undergo metastasectomy

-> Referral to medical oncology for palliative chemotherapy according to the current standard;

-> Referral to radiotherapy when palliative radiation is clinically considered

When no liver and lung metastases are found on CT scan

-> CEA measurement as before

-> Next step dependent on outcome, to discuss in interdisciplinary platform

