### *8.1.2. Secondary study parameters/endpoints*

Calculation of the optimal threshold values and measurement frequency of CEA by

means of calculating ROC curves based on actually measured CEA values.

Percentage of patients that show metastasis on CT thorax/abdomen when the rise of CEA at the chosen threshold values is above normal, and percentage of patients that do not show metastasis on CT thorax/abdomen despite rise of CEA.

Percentage of patients that show metastasis on regular CT Thorax/abdomen with no rise of CEA above normal (false negative rate of CEA measurement)

Overall survival, disease-free survival and recurrence-free survival

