## *Study procedures*

## Vena puncture bi-monthly: measurement serum CEA and serum ‘in storage’

## Vena punctures are carried out at local laboratories.

## CT scan abdomen/thorax

## At year 1 (abdomen) and 2 (thorax/abdomen)

## If CEA rises as outlined in the flowchart, a CT scan thorax/abdomen will be performed because of the suspicion for local recurrence or metastatic disease. If this scan is made coincidently at or around year 1, 2 or 3, the standard scan will be cancelled.

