2. Only when the patient is fit enough for metastasectomy, follow-up is started. This is assessed at the first outpatient visit and if necessary delayed at the surgeon’s judgment. [↑](#footnote-ref-3)
3. When a patient underwent a CT thorax/abdomen due to a rise in CEA during follow-up, the study CT at year 1 and 2 will not be made. [↑](#footnote-ref-4)
4. When a full colonoscopy has been performed pre-operatively, the colonoscopy at year 1 is not indicated. [↑](#footnote-ref-5)

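### The CEA false-negative rate in section 8.1.2 is, as written, the yield of regular CT in patients without a CEA rise, not missed recurrences over all recurrences

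*Protocol*

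**What the plan says.** Protocol section 8.1.2 plans two kinds of CEA accuracy figure that bear on this point.

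- For patients with a rise: "Percentage of patients that show metastasis on CT thorax/abdomen when the rise of CEA at the chosen threshold values is above normal", together with its complement, the patients whose CT is clear despite a rise.
- For patients without a rise: "Percentage of patients that show metastasis on regular CT Thorax/abdomen with no rise of CEA above normal (false negative rate of CEA measurement").

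Section 7.2.1 sends a confirmed rise to an extra CT. The first step is an increase of more than 20% in 8 weeks. The second is "Increase in second measurement after 4 weeks > 10%, with a lower static threshold value of 2.5 ng/ml".

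Two places say what then happens to the scheduled scan. Section 8.2 (Study procedures), on the triggered scan: "If this scan is made coincidently at or around year 1, 2 or 3, the standard scan will be cancelled". Footnote 3, on patients who had a CT because of a CEA rise during follow-up: "the study CT at year 1 and 2 will not be made".

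Section 8.2 gives the regular scans as "At year 1 (abdomen) and 2 (thorax/abdomen"); section 7.2 also lists one at year 3.

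**The concern.** The bracketed label names one quantity and the definition describes another. A false-negative rate conditions on having a recurrence: of all recurrences, how many did CEA miss? The definition conditions on the route of detection, because only metastases seen on a regular CT are eligible.

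This removes cases from both parts of the fraction. Recurrences that CEA detected belong in the denominator, but they are mostly found on the triggered CT, reported in the companion percentage, and often have no later regular CT. Silent recurrences that come to light through complaints between scans belong in the numerator and the denominator, but are not found on a regular CT. The year 1 regular CT covers the abdomen only, so a silent lung metastasis cannot be seen on it.

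The objective (section 3) is a guideline built on CEA and CT. The introduction justifies imaging by the recurrences that CEA does not signal early, and says that the optimal imaging frequency is unknown. The share of recurrences that CEA misses bears directly on that question. A yield published under the name of a false-negative rate would make CEA look better than it is.

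**Working it through.** **The plan's own figures.** The protocol states no CEA sensitivity or false-negative rate, so only the sample-size chain in section 6.4 can be reproduced. A two-sided 5% test of 10% against 25% with 80% power and continuity correction needs 113 patients with metastases per group, close to the stated 115. Then 115 / 0.25 = 460, and 460 x 1.71 = 786.6, which the protocol rounds to about 800.

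**Inputs.** From section 6.4: N = 800 patients, and recurrence 25% ("the expected occurrence of metachronous metastases is approximately 25" per cent), so R = 200 recurrences and 600 patients without. Assumed, because the documents give no values: CEA sensitivity (Se) 40-90%, specificity (Sp) 80-100%, the share *s* of silent recurrences that present between scans, and a regular CT for every patient who has neither a rise nor an earlier diagnosis.

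**Formulas.**

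- Missed recurrences: FN = R x (1 - Se). True false-negative rate: FN / R = 1 - Se.
- Reading A, per patient scanned without a rise: FN(1 - s) / [FN(1 - s) + 600 x Sp].
- Reading B, per patient in the group: FN(1 - s) / 800.
- Reading C, per metastasis seen on regular CT: FN / [FN + *l* x (R - FN)], where *l* is the share of CEA-detected recurrences that still reach a regular CT, with s = 0.

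**Reading A at s = 0**

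| Se | FN | True rate | A, Sp 100% | Too low by | A, Sp 80% | Too low by |
|---|---|---|---|---|---|---|
| 40% | 120 | 60% | 120/720 = 16.7% | 3.6 | 120/600 = 20.0% | 3.0 |
| 70% | 60 | 30% | 60/660 = 9.1% | 3.3 | 60/540 = 11.1% | 2.7 |
| 90% | 20 | 10% | 20/620 = 3.2% | 3.1 | 20/500 = 4.0% | 2.5 |

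**Presentation between scans.** At s = 20% and Sp 100%, A becomes 96/696 = 13.8%, 48/648 = 7.4% and 16/616 = 2.6% for the three sensitivities, which is 4.35, 4.05 and 3.85 times too low.

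**Reading B at s = 0.** At Se 70%, 60/800 = 7.5%. The factor is 1/0.25 = 4 at every sensitivity.

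**Reading C at Se 70% (true rate 30%).** With l = 0, 60/60 = 100%. With l = 10%, 60/74 = 81%. With l = 25%, 60/95 = 63%. With l = 50%, 60/130 = 46%. Only l = 100% returns 60/200 = 30%.

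**Sensitivity to the recurrence rate (reading A, Se 70%, Sp 100%, s = 0).** At 10% recurrence, 24/744 = 3.2%, 9.3 times too low. At 40%, 96/576 = 16.7%, 1.8 times too low.

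**All recurrences as denominator.** At Se 70%, 60/200 = 30%, which is correct at s = 0. At s = 20%, the restriction to regular CT leaves 48/200 = 24%, 1.25 times too low.

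**The case against.** **The denominator is open.** The text says only that it is a percentage of patients. Guided by the label, an analyst could divide by all patients with recurrence, and a statistical analysis plan might say so. This stands in part: that choice would remove most of the error. It would not restore silent recurrences found between scans, because the numerator is explicitly limited to regular CT. The point is therefore a stated quantity with the wrong name, not a missing detail.

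**The ROC curves already give sensitivity.** Section 8.1.2 plans them on measured CEA values, so an estimate of 1 minus the false-negative rate may appear elsewhere. That is fair, but it does not correct the parameter that carries the name.

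**A reader might infer that CEA-detected recurrences never enter the regular-CT set, so that the figure per metastasis is 100% by construction.** The documents do not support that. Section 8.2 cancels the standard scan only when the triggered one falls near a scheduled time, which is narrower than footnote 3. Moreover, a rise above normal in section 8.1.2 is not tied to the two-step rule of section 7.2.1. A patient whose rise was unconfirmed, awaiting repeat or attributed to infection could still have a regular CT that shows metastasis.

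**A reader might also put a fixed figure, such as four to five times too low, on the error.** That range needs perfect specificity and 30% of silent recurrences presenting between scans: at sensitivity 50/70/90%, 70/670 = 10.4%, 42/642 = 6.5% and 14/614 = 2.3%. With 0% the factors are 3.1 to 3.5; with 50% (50/650, 30/630, 10/610) they are 6.1 to 6.5. None of these inputs is in the protocol. The 25% may also not apply to the intervention period: hospitals cross over between January 2011 and January 2012, the window closes in October 2012, and patients up to three years after surgery enter.

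**Conclusion.** The point holds in a limited form. On its natural reading the parameter is the yield of regular CT in patients without a CEA rise, about 1 minus the negative predictive value. It is not the proportion of recurrences that CEA misses.

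At the protocol's 25% recurrence rate, with sensitivity 40-90%, specificity 80-100% and no presentation between scans, it would be roughly 2.5 to 3.6 times too low per patient scanned without a rise, and lower still if silent recurrences surface between scans. Read per metastasis on regular CT, it errs the other way: 63% to 100% against a true 30% at sensitivity 70%, if between a quarter and none of the CEA-detected recurrences still reach a regular CT. The direction on each reading follows from the design; the size depends on these assumptions.

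This is a descriptive secondary parameter. The primary endpoint, main analysis and sample size are unaffected. It is worth correcting because the figure bears on the recommendation the trial is meant to produce, and the correction is cheap.

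**What to change.** 1. In section 8.1.2, keep the present percentage but rename it *yield of regular CT in patients without a CEA rise*, with patients who had a regular CT and no rise as its denominator.
2. Add the false-negative rate: patients with a confirmed recurrence by any route in the intervention period who had no CEA rise within a stated window before diagnosis, divided by all patients with a confirmed recurrence in that period.
3. Use one stated definition of a CEA rise for this rate and for the companion percentages in patients with a rise. State the window, so that a rise long before diagnosis with a clear CT does not count as a detection.
4. Record the route of detection for each recurrence (triggered CT, regular CT, symptoms, other imaging). Sections 8.1.2 and 8.1.3 do not list it.
5. Reconcile section 8.2 with footnote 3 on when the regular CT is omitted, since this decides who is in the regular-CT set.

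The cost is a wording change in section 8.1.2, matching text in any statistical analysis plan, and one small added data item. The correction to the parameter itself requires no change to randomisation, visits or sample size.

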### *8.1.3. Other study parameters*

Co-morbidity influencing CEA: Smoking, benign gastro-intestinal disorders

Incidence of second primary malignancies that cause a rise in CEA

Patient characteristics

Tumour characteristics

Pre-operative CEA and CT thorax/abdomen (cTNM stage)

## *Study procedures*

## Vena puncture bi-monthly: measurement serum CEA and serum ‘in storage’

## Vena punctures are carried out at local laboratories.

## CT scan abdomen/thorax

## At year 1 (abdomen) and 2 (thorax/abdomen)

## If CEA rises as outlined in the flowchart, a CT scan thorax/abdomen will be performed because of the suspicion for local recurrence or metastatic disease. If this scan is made coincidently at or around year 1, 2 or 3, the standard scan will be cancelled.

## *8.3. Withdrawal of individual subjects*

Subjects can leave the study at any time for any reason if they wish to do so without any consequences. The investigator can decide to withdraw a subject from the study for urgent medical reasons.

## *8.4. Replacement of individual subjects after withdrawal*

Not applicable

## *8.5. Follow-up of subjects withdrawn from study*

Patients withdrawn from the study will be treated according to the common clinical practice (that is, regular follow-up) and their characteristics (incidence of metastasis, curative treatment) will be followed. They will be asked for reasons from withdrawal to gain insight in possible undesired effects of the intensified follow-up protocol.

## *8.6 Premature termination of the study*

## Premature termination of the study will be carried out when the follow-up according to the current guideline cannot be guaranteed.

## 9. SAFETY REPORTING

## *9.1. Section 10 WMO event*

In accordance to section 10, subsection 1, of the WMO, the investigator will inform the subjects and the reviewing accredited METC if anything occurs, on the basis of which it appears that the disadvantages of participation may be significantly greater than was foreseen in the research proposal. The study will be suspended pending further review by the accredited METC, except insofar as suspension would jeopardize the subjects’ health. The investigator will take care that all subjects are kept informed.

## *9.2. Adverse and serious adverse events*

Adverse events are defined as any undesirable experience occurring to a subject during a clinical trial. All adverse events reported spontaneously by the subject or observed by the investiga­tor or his staff will be recorded.

A serious adverse event is any untoward medical occurrence or effect that at any dose results in death;

- is life threatening (at the time of the event);
- requires hospitalization or prolongation of existing inpatients’ hospitalization;
- results in persistent or significant disability or incapacity;
- is a congenital anomaly or birth defect;
- is a new event of the trial likely to affect the safety of the subjects, such as an unexpected outcome of an adverse reaction, lack of efficacy of an IMP used for the treatment of a life threatening disease, major safety finding from a newly completed animal study, etc.

All SAEs will be reported to the accredited METC that approved the protocol, according to the requirements of that METC.

Anticipated adverse events

- Haematoma from vena puncture
- Anxiety caused by frequent vena punctures

## *9.3. Follow-up of adverse events*

All adverse events will be followed until they have abated, or until a stable situation has been reached. Depending on the event, follow up may require additional tests or medical procedures as indicated, and/or referral to the general physician or a medical specialist.

## *9.4. Data Safety Monitoring Board (DSMB)*

Not applicable

# 10.STATISTICAL ANALYSIS

In the clinical study, the main analysis will be based on the differences between care as usual (pre-treatment) and care after implementation of the CEA watch (post-treatment) regarding the percentage of patients with resected metastases, using a multilevel model to adjust for the clustering. For the quality of life data the same analysis will be applied. In addition, potential confounders such as age, gender and tumour status will be considered.

In an economic evaluation, costs and outcomes of both follow-up strategies will be assessed and compared. Research question in the economic evaluation: “What is the incremental cost-effectiveness of a computer based (CEA-watch) follow-up protocol, compared to follow-up care as usual?” Results of the cost-effectiveness analysis will display the additional costs per additional patient with curative metastasectomy. In addition, a cost-utility analysis will be conducted, based on the quality adjusted life years (QALYs). Both types of analyses will be conducted in order to be able to estimate the balance between costs and effects on health, survival and quality of life. Costs will be studied from a societal perspective, during a time period maximally 3 years. Since the time horizon of the study exceeds one year, both costs and effects beyond the first year will be discounted, using various discounting rates of 3%, 4% and 5%, and no discounting, to facilitate international comparison of study results.

Bootstrapping will be performed on the cost and effect pairs in order to calculate confidence intervals. Cost effectiveness acceptability curves will be constructed to illustrate the probability that the different follow-up strategies will be cost-effective, given different monetary values per additional unit of health (patient with patient with curative metastasectomy/QALY).

Relevant cost components of both follow-up strategies will be assessed for all included patients. Main cost categories will be ultrasound, CT-scan, colonoscopy, CEA assay, ‘CEA watch’ system, additional diagnostic tests, outpatient visits, hospital admissions and travel expenses.

Costs of productivity losses will not be taken into account, since the target population largely consists of retired people. Unit costs will be valued using Dutch standard prices. In case no standard prices are available, costs will be calculated according to the Dutch guidelines for cost studies (CVZ) . Volumes on cost categories will be registered on a patient level, except for travelling expenses, for which a question will be added to the Quality of Life questionnaire.

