The innovative element of the study is the introduction of CEA watch. This intranet based program based on open source software: MySQL database, PHP scripting and java. It automatically presents new CEA values of enlisted patient to the interpreting doctor. Normal results of CEA can immediately be sent by e-mail to the patient. A suggestion for a date for a new CEA check is made based on available information. In the case of a rise in CEA the patient will be called and appropriate steps will be made. All results will be sent to the patients by postal mail as well, with a laboratory form for the next CEA check. For this next CEA check the patient can report to the hospital laboratory at a date or time by his own choosing. If a patient seems to forget a CEA check, CEA-watch will issue a reminder. CEA-watch has several advantages for the patient and for the clinic. Outpatient clinic visits are reduced. The patient will come to the outpatient clinic only once a year if the results are normal. This will reduce concerns to the outcome of the disease by the patient and his family, as every outpatient clinic visit is a renewed confrontation with the disease. Furthermore, it will reduce the workload for the outpatient clinic. Compliance to the schedule of frequent testing is achieved by constant monitoring of every individual patient. Patient satisfaction is expected to increase due to the early availability of the result and the reduction of waiting time in the hospital since the patient only has to come to the laboratory at a moment chosen by him. The relevant clinical outcome is the increase in the number of radical resected metastases (lung, liver and peritoneal cavity) with a subsequent increase in cancer-specific survival.

*2.5. Imaging*

CT scanning may be superior to ultrasound in terms of sensitivity, specificity and inter- and intraobserver reliability, but it is more expensive than ultrasound and related to radiation-based health hazards. As the optimal frequency for imaging is not known, it may be expected that the use of ultrasound and CT will increase as will the logistical and financial consequences of its use without known efficacy.

*2.6. Previous studies by our group*

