**5. STUDY DESIGN**

This trial is a randomized national multicentre study comparing intensified and conventional follow-up schedule for patients after curative treatment of colorectal cancer. The inclusion is during maximal 2.5 years or until 2000 patients are included. Total expected duration 3 years. Patients may enter during their first three years after curative treatment[[1]](#footnote-2) of colorectal cancer.

The study is constructed with the stepped-wedge design. This implies a randomization at hospital level. The surgeons in a hospital control all their eligible patients according to the care as usual. At the moment determined by the randomization, all included patients will change to the intensified study follow-up protocol. As a result, the early-randomized hospitals have a large amount of patients in the study group and a small amount of patients in the control group, where in the late-randomized hospitals it is the other way around. Randomization will take place on July 1st, 2010 and randomization will be performed per two hospitals. The firstly randomized hospitals start with the intensified follow-up scheme on January 1st, 2011 and since ten hospital will participate, the last two hospitals start with the intensified follow-up scheme at January 1st, 2012.

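### The stated main analysis of the stepped wedge is a pre/post contrast in a multilevel model for clustering and names no adjustment for calendar time, so it does not separate the CEA-watch effect from a secular trend

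*Protocol*

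**What the plan says.** Section 5 fixes the design: "The study is constructed with the stepped-wedge design. This implies a randomization at hospital level". Ten hospitals cross in pairs ("randomization will be performed per two hospitals"). The first pair starts on 1 January 2011, and "the last two hospitals start with the intensified follow-up scheme at January 1st, 2012". The Summary puts three months between steps. The crossing is in one direction and covers everyone under follow-up: at the hospital's date "all included patients will change to the intensified study follow-up protocol". Section 8.1.1 sets the window for the primary outcome at July 2010 to October 2012.

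Section 10 describes the main analysis in one sentence. The contrast is pre versus post: "the main analysis will be based on the differences between care as usual (pre-treatment) and care after implementation of the CEA watch (post-treatment"). The model is described by its purpose: "using a multilevel model to adjust for the clustering". The quality-of-life data get the same analysis. A further sentence adds that "potential confounders such as age, gender and tumour status will be considered". Calendar time, period, step and secular trend are not named as model terms anywhere in the protocol.

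Section 6.4 plans for 10% versus 25% resected among patients with metastases. It inflates the sample size by a factor of 1.71, based on a between-hospital SD of 0.1. It makes no allowance for time effects.

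**The concern.** In a one-way stepped wedge the intervention always comes later than control in the same hospital, so exposure and calendar time are confounded by construction. Randomising the order of the hospitals makes it possible to separate the two, because in the middle of the trial some hospitals have crossed and others have not. An analysis achieves that separation only if time is in the model. A random hospital effect removes stable differences between hospitals. It does not remove a change over time that is common to all of them, and neither do age, gender or tumour status.

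If imaging, referral or surgical practice changed between 2010 and 2012 in a way that raised the percentage resected, the stated model would credit that rise to CEA watch. A falling trend would hide a real effect. The primary estimate, its type I error and the quality-of-life comparison are all exposed.

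**Working it through.** **The plan's own sample size first.** For 10% versus 25%, two-sided 5% (sidedness is not stated, so this is assumed) and 80% power, the standard two-proportion formula gives 100 per group, or 113 with continuity correction, against the stated 115. Then 115 / 0.25 = 460, and 460 × 1.71 = 786.6, stated as about 800. The factor 1.71 matches a parallel-cluster design effect with 115 / 10 = 11.5 recurrences per hospital per condition: 1 + (11.5 − 1) × 0.01 / (0.13875 + 0.01) = 1.71. That match is an inference, since the cited source is not at hand. The formula contains no time effects.

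**How far time and condition overlap.** July 2010 to October 2012 is taken as 27 months (9 quarters). Pairs cross at s = 6, 9, 12, 15 and 18 months.

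- Gap within a hospital between the mean times of the two conditions: (s + 27)/2 − s/2 = 13.5 months, whatever s is. A window of 8 or 10 quarters would give 12 or 15 months.
- Control hospital-months: 2 × (6 + 9 + 12 + 15 + 18) = 120. Of these, 10 × 6 = 60 (50%) fall before any hospital has crossed.
- Intervention hospital-months: 270 − 120 = 150. Of these, 10 × 9 = 90 (60%) fall after all hospitals have crossed.
- Only the 12 months of 2011 have both conditions running.

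**Effect of a trend on the stated model.** Inputs: 10 hospitals × 9 quarters with equal cells; 400 recurrences (2 × 800 × 25%); hospital SD 0.1 (Section 6.4); within-hospital variance (0.10 × 0.90 + 0.25 × 0.75)/2 = 0.139. The method is generalised least squares on the cell means with a random hospital intercept and no time term. The standard error is 0.039, and the bias is 1.09 times the yearly trend. Type I error is Φ(b/SE − 1.96) + Φ(−b/SE − 1.96), where b is the bias. The trends are assumed, because the protocol gives none.

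| Assumed trend, points per year | Spurious effect, points | Two-sided type I error |
|---|---|---|
| 1 | 1.1 | 5.9% |
| 2 | 2.2 | 8.7% |
| 3 | 3.3 | 13.4% |
| 5 | 5.5 | 28.9% |

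The result does not hinge on the hospital SD: at an SD of 0 or 0.05 the bias is still 1.01 or 1.06 times the yearly trend.

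**Effect of adding time.** With a fixed effect for each quarter, the bias from a common trend is zero. The price is precision:

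- Without time, 400 recurrences: SE 0.039; power Φ(0.15/0.039 − 1.96) = 97%.
- With quarter effects, 400 recurrences: SE 0.070; power Φ(0.15/0.070 − 1.96) = 57%.
- With quarter effects at the cap of 2,000 patients in Section 5 (2,000 × 25% = 500 recurrences): power about 66%.
- With an added hospital-by-period SD of 0.05 or 0.10 (assumed), 400 recurrences: SE about 0.073 or 0.080; power about 54% or 47%.

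Using 0.175 × 0.825 = 0.144 as the within-hospital variance changes little: power with quarter effects is 56% at 400 recurrences and 64% at 500. On that variance, 80% power would need about 740 recurrences, or about 2,960 patients at a 25% recurrence rate.

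**The case against.** The strongest reply is that Section 10 is a short protocol paragraph. Its list of confounders is open-ended, nothing in it excludes calendar time, and a statistical analysis plan that is not at hand may supply the full model. This has weight. A reader might infer that the protocol adjusts for clustering and nothing else, but the sentence on potential confounders does not support that. What stands is narrower: the examples given are all patient or tumour factors, and the protocol itself states the main contrast as pre versus post without naming time. A later plan that added period would be supplying what this design most needs and the protocol leaves out.

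Three other strong readings go beyond the text.

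- Section 2.5 remarks that "it may be expected that the use of ultrasound and CT will increase". A reader might take this as the protocol's own forecast of a trend in usual care during the trial. It names neither usual care nor these years, and it says nothing about the percentage resected, which is the trend that matters here.
- A reader might conclude that the analysis makes no use of the randomised start dates. A random-intercept model does draw on some between-hospital contrast during 2011. The accurate statement is that it does not separate time from treatment.
- A reader might treat the table above as bias that has been shown. It is conditional on assumed trends. At 1 point per year the damage is slight, and 5 points per year would be a 50% relative rise in one year on a 10% control rate.

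It is also fair to say that nine period effects plus a hospital-by-period variance is a heavy model here: 400 recurrences over 90 hospital-quarters is about 4.4 per cell. That limits how detailed the remedy should be. It does not remove the need for one.

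**Conclusion.** The point holds in this form. Followed as written, the main analysis passes a secular trend common to all hospitals into the primary estimate, at about 1.09 times the yearly trend. Trends of 1 to 5 points per year would produce a spurious effect of about 1.1 to 5.5 points, against a planned difference of 15, and a type I error of about 6% to 29%. The protocol neither states nor implies that such a trend exists, so this is an unprotected analysis and not a demonstrated bias.

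The figures assume recurrences spread evenly over hospitals and quarters, 400 recurrences, a hospital SD of 0.1, a linear-probability approximation and normal-theory tests. The last of these is optimistic with ten hospitals. Since the same patients cross over, time since surgery also differs between the conditions, and calendar terms alone may not remove that.

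The high power of the unadjusted model (about 97%) depends on assuming that there is no trend.

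**What to change.** In Section 10, state the primary model as a multilevel model with a random hospital effect and an adjustment for calendar time. Use fixed effects for the 3-month steps, or a smoother time term if the cells prove too sparse. A linear term removes a linear trend at a slightly smaller standard error, about 6.6 to 6.8 points depending on the within-hospital variance used. Take the intervention effect from that model, with small-sample inference suited to ten hospitals, for example adjusted degrees of freedom or permutation of the randomised order of the pairs. Apply the same model to the quality-of-life data. A random hospital-by-period effect is optional, as a sensitivity analysis. The unadjusted pre/post contrast can be kept as description.

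No new data are needed, since the calendar dates follow from the design, but the change is more than a matter of wording. With fixed quarter effects the standard error rises from about 3.9 to 7.0 points. Power for 10% versus 25% falls to about 57% at 400 recurrences and about 66% at the 2,000-patient cap, and lower with hospital-by-period variation. Section 6.4 should therefore be recomputed and its power restated for the time-adjusted model.
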